# Focal vs extended ablation in localized prostate cancer with irreversible electroporation; a multi-center randomized controlled trial

**DOI:** 10.1186/s12885-016-2332-z

**Published:** 2016-05-05

**Keywords:** Irreversible electroporation, IRE, Prostate cancer, Localized, Focal therapy, Ablation, Randomized controlled trial

## Abstract

**Background:**

Current surgical and ablative treatment options for prostate cancer (PCa) may result in a high incidence of (temporary) incontinence, erectile dysfunction and/or bowel damage. These side effects are due to procedure related effects on adjacent structures including blood vessels, bowel, urethra and/or neurovascular bundle. Ablation with irreversible electroporation (IRE) has shown to be effective and safe in destroying PCa cells and also has the potential advantage of sparing surrounding tissue and vital structures, resulting in less impaired functional outcomes and maintaining men’s quality of life.

**Methods/Design:**

In this randomized controlled trial (RCT) on IRE in localized PCa, 200 patients with organ-confined, unilateral (T1c-T2b) low- to intermediate-risk PCa (Gleason sum score 6 and 7) on transperineal template-mapping biopsies (TTMB) will be included. Patients will be randomized into focal or extended ablation of cancer foci with IRE. Oncological efficacy will be determined by multiparametric Magnetic Resonance Imaging, Contrast-Enhanced Ultrasound imaging if available, TTMP and Prostate Specific Antigen (PSA) follow-up. Patients will be evaluated up to 5 years on functional outcomes and quality of life with the use of standardized questionnaires.

**Discussion:**

There is critical need of larger, standardized RCTs evaluating long-term oncological and functional outcomes before introducing IRE and other focal therapy modalities as an accepted and safe therapeutic option for PCa. This RCT will provide important short- and long-term data and elucidates the differences between focal or extended ablation of localized, unilateral low- to intermediate-risk PCa with IRE.

**Trial registration:**

Clinicaltrials.gov database registration number NCT01835977. The Dutch Central Committee on Research Involving Human Subjects registration number NL50791.018.14.

## Background

Prostate cancer (PCa) is the most common cancer in men and the second leading cancer-related cause of death. The incidence of PCa increases steadily, contributors to this increasing incidence include the ageing population, increased awareness and implementation of the Prostate Specific Antigen (PSA) test [1]. Due to the increasing use of the PSA test and improved diagnostic technology more patients with early stage, localized PCa are diagnosed nowadays.

### Present therapeutic options by guideline

Currently, there are several treatment options available for PCa, including surgery, radiotherapy, minimally invasive ablative techniques and active surveillance. Choice of treatment depends on patients’ choice and risk stratification (e.g. D’Amico Risk Classifications [2]). Active surveillance is an attractive management option for (very) low-risk PCa. Especially older men, who have the highest incidence of PCa [1], may be suitable candidates for active surveillance (AS) since these patients have a limited life-expectancy and may have co-morbidities. AS can have an impact on quality of life since patients do not receive treatment for their cancer and sometimes the window of opportunity to treat curatively can be missed. For localized disease, a radical prostatectomy or radiotherapy are the recommended curative treatments according to the guidelines [3–5]. The most common side effects associated with radical treatments are: erectile dysfunction (58–79 %), gastrointestinal toxicity and proctopathy (13–34 %), incontinence (range 3.2–14 %), overactive and/or obstructive urinary symptoms and hematuria (5 %) [6, 7]. It is the result of procedure-related damage to blood vessels, bowel, urethra and/or neurovascular bundle and may impair the quality of life in PCa patients following treatment [6].

### Focal therapy for localized prostate cancer

The side effect profile of radical treatments opened the door to focal strategies that limit damage to the important anatomical urological structures [8, 9]. A variety of ablation techniques have been used, including cryoablation, high-intensity focused US (HIFU), radiofrequency ablation (RFA), microwave coagulation, Vascular Targeted Photodynamic Therapy, Interstitial Laser Thermotherapy and Irreversible Electroporation (IRE) [10]. Focal therapy gained popularity because of the minimally invasive approach, short hospital stay, possible improved functional outcomes, lower complication rate and less impact on the quality of life [10]. Moreover, focal treatment provides a more curable treatment option compared to active surveillance and is better tolerated than radical treatments by older patients with comorbidities. A systematic review on focal treatment by *Valerio* et al. has been published, comprising a total of 2350 cases across 30 studies with a follow-up range between 0 and 11.1 year. In PCa initially treated with focal therapy, the pad-free continence ranged from 95 to 100 %, retained erectile function ranged from 54 to 100 % and PCa was absent in 50 to 96 % on regular follow up biopsies [10]. *Cheetham* and colleagues [11] published promising long-term survival rates of patients undergoing primary or salvage cryotherapy for PCa. Results indicated an 87 % overall 10-year prostate-cancer-specific survival, despite early cryotherapy technology and the majority of patients having high-risk PCa.

### Irreversible electroporation for prostate cancer

Electroporation is a technique in which high-frequent electric pulses are generated between two or more electrodes. The resultant electric current damages the cell membrane, allowing molecules to pass into the cell passively. The process of electroporation can either be temporary (reversible electroporation) or become permanent (IRE) when a certain electric threshold is reached, causing cell death due to the inability to maintain homeostasis [11–13]. Initially, the occurrence of IRE during reversible electroporation procedures was considered an unwanted side effect. However, the ability of IRE to induced selective cell death turned IRE into a tumour ablation modality, leading to the development of the commercially available Nanoknife™ (AngioDynamics, Queensbury, New York) [12]. Histopathological outcomes after IRE show a sharp demarcation between ablated and non-ablated tissue, whereas thermal ablation techniques show a transitional zone of partially damaged tissue due to insufficient temperatures for definitive ablation [14]. Therefore, IRE tissue ablation possibly enables more precise procedure planning of the target area. IRE has shown to effectively ablate tumour cells in vitro, in animal studies and in phase 1–2 human trials on IRE (cancer) ablation in several organs (liver, pancreas, kidney, lung and prostate) [15–18]. The first phase 1–2 trials on focal therapy of PCa with IRE have shown promising results, demonstrating a safe and effective focal treatment modality with low patient morbidity, improved functional outcomes and good short-term oncological control [14, 19–22]. No major complications occurred in any of these trials. All of the patients that were continent before the IRE procedure remained pad-free continent, whereas erectile function was preserved in 56 to 95 % of patients that were potent before [21, 22]. In the Phase I-II trial on IRE conducted by the Clinical Research Office of the Endourological Society (CROES) [14], IRE was performed in sixteen patients 30 days prior to their scheduled radical prostatectomy. The histopathological assessment of the prostate showed sharply demarcated necrotic and fibrotic lesions, without skip lesions [14]. This is in concordance with the other phase 1–2 trials with the exception of the study of *Valerio* et al. where 6/34 patients had possible residual tumour within the ablation zone on multiparametric Magnetic Resonance Imaging (mpMRI) [21]. In the aforementioned study, *van den Bos* et al. performed Transrectal Ultrasound (TRUS), mpMRI and Contrast-Enhanced Ultrasound (CEUS) imaging following IRE to evaluate the ability of the imaging modalities to accurately visualize IRE ablation effects, ablated area and possible residual PCa. Both mpMRI and CEUS were found to be feasible imaging modalities with concordance in volume to the ablated volume on histopathology with Pearson’s correlation of *r* = 0.88 and *r* = 0.80, respectively [23].

At present, no randomized controlled trial (RCT) (grade 2b) on IRE for treatment-naïve PCa has been conducted. Moreover, no long-term evidence is available on functional and oncological outcomes following IRE treatment in PCa. In this RCT (NCT01835977) 200 patients with histologically confirmed (on TTMB), organ-confined and unilateral low- to intermediate-risk (Gleason score 6 or 7) PCa will receive ultrasound-guided IRE. Selected candidates will be randomized to either 1) focal ablation or 2) extended hemiablation of the tumour lesions to assess the differences in side effect profile and efficacy of the treatment and to investigate if an extended ablation zone is necessary to treat undetected satellite lesions adjacent to the index lesion (Fig. 1) [24]. Patients will be evaluated on urinary continence, erectile function and quality of life with the use of standardized questionnaires [25–27]. Oncological efficacy will be determined by TTMP, preceded by mpMRI and CEUS imaging if available and PSA follow up.

**Fig. 1 Fig1:**
[figure not shown]
The Different Ablation Treatments. **a** Focal Ablation of a PCa lesion in Group A. **b** Extended Ablation of a PCa lesion in Group B

## Methods/Design

### Study objectives

#### Primary

To evaluate the differences in side effects of patients treated with focal vs extended ablation of PCa with IRE, measured by CTCAE, IIEF, IPSS and use of pads.To evaluate the differences in quality of life of patients treated with focal vs extended ablation of PCa with IRE, measured by EPIC, VAS pain score and length of hospital stay.

#### Secondary

To evaluate the oncological efficacy of IRE for focal vs extended ablation of PCa, measured by TTMB 6 months after IRE and 5 year follow-up with mpMRI and serial PSA testing.To evaluate the utilization of mpMRI in the oncological follow up after IRE ablation of PCa and to visualize the extend of the ablation zone, performed 6 months and 1, 2, 3, 4 and 5 years following the IRE procedure.If available, to evaluate the utilization of CEUS in the oncological follow up following IRE ablation of PCa and to visualize the extend of the ablation zone, performed 6 months and 1, 2, 3, 4 and 5 years following the IRE procedure.

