### Study design

In this prospective RCT, patients with unilateral PCa (clinical stage T1c-T2b), confirmed on transrectal ultrasound(TRUS)-guided biopsies, will be offered extensive (30-core) TTMB. If the inclusion criteria are met (see below and Table 1), candidates are randomized into two groups. One group will undergo a focal ablation of the prostate (Group A), the other group will receive an extended hemi ablation (Group B) (Fig. 1). Prior to the procedure, a baseline mpMRI, TRUS and CEUS imaging (if available) will be obtained and standardized questionnaires (International Prostate Symptom Score (IPSS), International Index of Erectile Function (IIEF), Quality of life-questionnaire (EPIC), Visual Analogue Scale (VAS)) and number of pads used will be completed by the patients (Fig. 2). After the focal or extended IRE ablation, follow-up will be performed following a strict schedule up to 5 years (Table 2) using mpMRI, TRUS and CEUS imaging (if available), blood tests (PSA, Creatinine), adverse event reporting with Common Terminology Criteria for Adverse Events (CTCAE) and the use of standardized questionnaires (IPSS, IIEF, EPIC, VAS). Six months following the IRE procedure patients will undergo TTMB to determine ablative effectiveness on pathology and to exclude any residual or ‘new’ disease. In case of any positive biopsies on follow-up TTMB, patients will be offered salvage treatment following the EAU Guidelines on Prostate Cancer [3].

**Table 1 Tab1:** Inclusion and exclusion criteria

Inclusion criteria	Exclusion criteria
1. Histologically confirmed organ-confined unilateral PCa on TTMB (clinical stage T1c-T2b)	1. Bleeding disorder (prothrombin time > 14.5 s., partial thromboplastin time > 34 s.), Platelet Count <140/uL, 2. No ability to stop anticoagulant or antiplatelet therapy
2. Gleason sum score 6 or 7	3. Active (urinary tract) infection 4. History of bladder neck contracture 5. Major concurrent debilitating illness or ASA ≥4 6. Cardiac History
3. PSA <15 ng/mL or PSA >15 ng/mL counselled with caution	7. Inflammatory bowel disease 8. Major rectal surgery 9. Previous radiation to pelvis 10. Prior or concurrent malignancy
4. Life expectancy of >10 years, age ≥18 years	11. Biologic or chemotherapy for PCa 12. Hormonal therapy within last 6 months 13. Any resection or stenting of the prostate 14. Prostate calcification >5 mm

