**Fig. 3 Fig3:**
[figure not shown]
**a** The Nanoknife console. **b** Specific ablation zone: with the needles placed 1.5 cm apart, the active electrode length is set at 2 cm and the resultant ablation volume is calculated at 12.75 cm^3^

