#### Multiparametric magnetic resonance imaging

mpMRI will be performed in supine position on a 1.5 T AVANTO® MRI scanner (Siemens Healthcare, Erlangen, Germany) using an integrated endorectal-pelvic phased-array coil (Medrad, Warrendale, USA). Prior to the mpMRI, anti-Peristaltic Drugs (Buscopan or Glucagon) will be given. T2 weighted sequences will be performed in sagittal, coronal and transverse planes from the aorta bifurcation to the pubic symphysis, including prostate and seminal vesicles. Next, T1 diffusion-weighted with fat suppression and dynamic contrast-enhanced images (0.1 mmol of gadopentetate dimeglumine per kg of body weight, Gadolinium DTPA, Gadovist) are obtained. mpMRI will be evaluated by a specialized uro-radiologist (blinded for the randomization) on prostate and ablation volume, evidence of residual or recurrent PCa according to the PIRADS (v2) criteria [31], skip lesions within the target zone, damage to adjacent structures and lymph node or haematogenous metastasis.

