#### Statistical analysis

Data will be collected using the Data Management System of CROES. The validated questionnaires will be analysed with standard methods. Maximum and minimum values will be set according to the extremes of questionnaire item scales. Categorical outcomes will be reported as point estimates with binomial 95 % CIs to demonstrate level of precision. Wilcoxon signed rank test (two-tailed) will be used to assess differences between continuous variables that were not normally distributed (PSA and questionnaire scores), measured at baseline and at the subsequent follow-up visit. Changes over time will be reported with box-and-whisker plots. The group analyses will be hypothesis-generating and we will run statistical tests of significance.

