In this trial TTMB is used to select patient for focal therapy in localized PCa, as recommended after an international consensus meeting [28]. However, special computer models of 3D whole mount prostatectomy specimens were compared in a small series (*n* = 25) to their corresponding TTMB cores. Eighteen out of sixty four lesions were missed (only 1 was clinically significant) by TTMB and sum Gleason score was upgraded in 12 % (*n* = 3) [30]. A concurrent study by *Hu* et al. showed the superiority of TTMB above TRUS-guided biopsies in diagnosing and staging PCa but TTMB regimen still missed 5 % of ≥0.2 mL and ≥0.5 mL lesions [29]. This highlights the confounding factor that TTMB has on accurate patient selection, treatment zone determination and oncological follow-up. In line, PCa foci may also be missed on mpMRI. mpMRI data (on a 1.5 T device) compared to whole mount prostatectomy specimen showed sensitivity/specificity and positive/negative predictive values for detection of PCa by mpMRI of 77/91 and 86 %/85 % for foci of >0.2 mL and 90/88 and 77 %/95 % for foci of >0.5 mL, respectively [37, 38]. However, in a recent study (*n* = 50) the combination of mpMRI with TTMB, used in a RCT, was found to have a high negative predictive value (91 %) for low-grade, small volume (>3 mm) PCa, indicating a reliable assessment to prevent undertreating significant PCa [39]. Since pathological assessment following IRE showed fibrosis without glandular prostatic ducts and necrotic tissue and no skip lesions within the ablated zone, we believe IRE effectively ablates all PCa foci within the target zone. Tumour ablation experiments in animals and humans have shown the potential to preserve connective tissue structures within the target zone and limit damage to associated blood vessels, neural tissue or other vital structures [16–18]. However, this may not apply to current thorough clinical treatment protocols [14, 40].

Therefore, in our opinion this RCT will provide important data on the differences between focal or extended ablation of localized, unilateral low- to intermediate-risk PCa using IRE, providing essential long-term data on functional outcome and oncological control.

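### Serial PSA is listed as a focal-versus-extended efficacy measure, but a between-arm reading of PSA level or fall would favour the extended arm even with equal cancer control

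*Protocol article*

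**What the plan says.** The first secondary objective of the protocol article sets focal against extended ablation on oncological efficacy, "measured by TTMB 6 months after IRE and 5 year follow-up with mpMRI and serial PSA testing". PSA is thus one of three named measures of a between-arm question.

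The Statistical analysis section gives one method for PSA: a two-tailed Wilcoxon signed rank test for "differences between continuous variables that were not normally distributed (PSA and questionnaire scores), measured at baseline and at the subsequent follow-up visit". That is a paired test within patients. The same section calls the group analyses hypothesis-generating and says that significance tests will be run, without naming a between-arm test for PSA.

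The randomised factor is the extent of ablation. Under Study design: "One group will undergo a focal ablation of the prostate (Group A), the other group will receive an extended hemi ablation (Group B". On what happens to treated tissue, the Discussion reports "fibrosis without glandular prostatic ducts and necrotic tissue and no skip lesions within the ablated zone".

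Table 2 schedules PSA at eleven follow-up visits (2 and 4 weeks, 3, 6, 12, 18, 24 and 30 months, and years 3, 4 and 5) and mpMRI at six (6 months and years 1 to 5). Follow-up template biopsy (TTMB) is scheduled once, at 6 months. The mpMRI is also read "on prostate and ablation volume", but nothing in the article links those volumes to PSA.

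**The concern.** PSA comes from benign prostate tissue as well as from cancer. That is general knowledge rather than a statement in the article, but the article does say that glandular tissue is lost where IRE is applied. A man whose ablation covers more of the gland should therefore show a larger fall in PSA, whether or not more of his cancer was destroyed.

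In most trials randomisation would balance the amount of benign gland between arms. Here it cannot, because the amount of gland destroyed is the randomised treatment. A between-arm comparison of PSA level, or of change from baseline, mixes treated volume with cancer control and leans towards the extended arm.

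The Background asks whether an extended zone is needed to treat undetected satellite lesions. A PSA advantage for the extended arm could be taken as a yes when it shows only that more gland was treated. Since biopsy is not scheduled again after 6 months, scheduled oncological follow-up from then on consists of mpMRI and PSA, with CEUS where available.

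**Working it through.** **No figure to reproduce.** The article gives no PSA effect, standard deviation, failure threshold or power. What follows shows direction and a range under stated assumptions.

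**Inputs**
- Example ablation volume: the Fig. 3 caption says "resultant ablation volume is calculated at 12.75" cm³. The caption does not state the arm; assigning it to the focal arm is an assumption.
- Extended ablation removes 50 % of the gland: assumption, from the word hemi-ablation.
- Gland volume V of 30 to 60 cm³: assumption.
- PSA proportional to remaining viable gland, and equal cancer control in both arms: assumptions.

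**Model.** Post-treatment PSA = baseline PSA × (1 − f), where f is the fraction of gland ablated. Focal f = 12.75/V; extended f = 0.50. Ratio of extended to focal PSA = 0.50/(1 − 12.75/V).

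| V (cm³) | Focal fall | Extended fall | Gap (points of baseline PSA) | Ratio extended/focal | Extended arm lower by |
|---|---|---|---|---|---|
| 30 | 42.5 % | 50 % | 7.5 | 0.50/0.575 = 0.87 | 13 % |
| 40 | 31.9 % | 50 % | 18.1 | 0.50/0.681 = 0.73 | 27 % |
| 50 | 25.5 % | 50 % | 24.5 | 0.50/0.745 = 0.67 | 33 % |
| 60 | 21.3 % | 50 % | 28.8 | 0.50/0.788 = 0.63 | 37 % |

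**A second set of assumptions.** Let focal ablation remove 15 to 35 % of the gland instead, against 50 %. The ratio is then 0.50/0.85 = 0.59 to 0.50/0.65 = 0.77. From an assumed baseline PSA of 6 ng/mL, follow-up PSA is 5.1 to 3.9 (focal) against 3.0 (extended), a gap of 2.1 to 0.9 ng/mL.

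**Where the effect disappears.** With 42.5 % against 45 % ablated, the ratio is 0.55/0.575 = 0.96. In the table's model the gap closes at V = 12.75/0.50 = 25.5 cm³.

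**Could a trial of this size show it?** The article specifies no such test, so this only illustrates what a two-sample comparison of log PSA would do. Take 90 men per arm (the number in the sample size section, which is powered on IIEF), two-sided α of 0.05 and an assumed SD s of log PSA. The chance of a significant result favouring the extended arm is Φ(|ln ratio|/(s√(2/90)) − 1.96).
- Ratio 0.77, s = 0.6: 0.262/0.0894 − 1.96 = 0.97, giving 0.84. With s = 0.8: 0.60.
- Ratio 0.59, s = 0.6: above 0.99. With s = 0.8: 0.99.
- Ratio 0.96, s from 0.8 to 0.4: 0.06 to 0.11, against 0.025 with no difference at all.

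**The case against.** The strongest reply is that the article never commits to comparing raw PSA between arms. The one named test is paired, so it cannot by itself favour either arm. The group analyses are called hypothesis-generating. How serial PSA becomes an efficacy measure (nadir, rise, failure definition) is the kind of detail that a full protocol or analysis plan supplies, and neither is shown. Five years of serial testing is also compatible with following each man from his own nadir.

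Much of this stands. A reader might infer that the plan prescribes a between-arm test of PSA change; the text does not say so. What remains is that PSA is fixed as a measure of a focal-versus-extended objective, and the only PSA analysis described uses levels at baseline and follow-up. Setting those within-patient changes side by side by arm is the natural way to meet that objective, and that is where the bias enters.

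A reader might also infer that the five-year oncological comparison is invalid. The documents do not support that. Biopsy is the first-named measure, and mpMRI is read centrally, blinded to the procedure, with PIRADS, at 6 months and yearly to 5 years. Neither shares this mechanism.

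The objection to the size is fair too. Gland volumes, strict proportionality, the 50 % figure and the arm of the Fig. 3 example are all assumed. The Background describes the extended zone in terms of satellites next to the index lesion, and Fig. 1 is not shown, so the two ablated volumes may lie closer together than a half-gland treatment suggests.

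**Conclusion.** The point holds in a limited form. Raw PSA level, or its change from baseline, is not a fair between-arm measure of cancer control when the arms are defined by how much gland is ablated. The lean towards the extended arm follows from the design, given that benign gland produces PSA.

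The size does not follow from the documents. Under the first set of assumptions extended-arm PSA would be about 13 to 37 % lower with identical cancer control; with similar ablated volumes the difference would be close to nil. No single figure in that range should be quoted as the expected bias.

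The reach is one of three measures of a secondary objective. The primary objectives and the sample size are untouched. The change is worth making because it is cheap and the error would bear on the trial's clinical question; it is not a flaw that undermines the trial.

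**What to change.** In the analysis wording:

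1. Base the between-arm oncological comparison on the 6-month TTMB, supported by the blinded mpMRI reads to 5 years.
2. State that raw PSA level and change from baseline will not be interpreted between arms as efficacy. Report them by arm descriptively, with a note that they reflect treated volume.
3. If PSA is to inform longer-term control, define it as change relative to each man's own post-ablation nadir. State that this reduces but does not remove the dependence on residual gland, since remaining benign tissue can still raise PSA.
4. Use volume-corrected PSA only as a sensitivity analysis. The mpMRI volumes make it possible, but residual volume is a post-randomisation quantity set by the treatment, viable gland must be separated from fibrosis, and the values exist only at mpMRI visits.

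No new visits or data are needed. The cost is that PSA, the most frequently scheduled oncological measurement, contributes less to the between-arm efficacy conclusion.
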